## Abstract

**Background:**

The total ankle replacement versus ankle arthrodesis (TARVA) trial aims to determine which surgical procedure confers the greatest improvement in pain-free function for patients with end-stage ankle osteoarthritis. Both procedures are effective but there has not yet been a direct comparison to establish which is superior. This article describes the statistical analysis plan for this trial as an update to the published protocol. It is written prior to the end of patient follow-up, while the outcome of the trial is still unknown.

**Design and methods:**

TARVA is a randomised, un-blinded, parallel group trial of total ankle replacement versus ankle arthrodesis. The primary outcome is the Manchester-Oxford Foot Questionnaire walking/standing domain score at 52 weeks post-surgery. Secondary outcomes include measures of pain, social interaction, physical function, quality of life, and range of motion. We describe in detail the statistical aspects of TARVA: the outcome measures, the sample size calculation, general analysis principles including treatment of missing data, the planned descriptive statistics and statistical models, and planned subgroup and sensitivity analyses.

**Discussion:**

The TARVA statistical analysis will provide comprehensive and precise information on the relative effectiveness of the two treatments. The plan will be implemented in January 2020 when follow-up for the trial is completed.

**Trial registration:**

ISRCTN registry number 60672307, ClinicalTrials.gov registration number NCT02128555. Registered 1 May 2014. Recruitment started in January 2015 and ended in January 2019.

## Background

End stage ankle osteoarthritis (OA) causes pain and chronic disability [1, 2]. It has been estimated that at least 29,000 patients with symptomatic ankle OA are referred to specialist foot and ankle surgeons each year in the UK, and that around 3,000 will choose to undergo surgery with the NHS [3]. The main surgical treatments for end-stage ankle OA are total ankle replacement (TAR) or ankle arthrodesis (fusion) [4]. Improvements in pain-free function and quality of life have been reported for both TAR and fusion, but there has never been a prospective randomised trial directly comparing the two treatments [5].

TARVA is a parallel-group, non-blinded randomised controlled trial that will compare clinical outcomes and cost-effectiveness of TAR versus ankle arthrodesis in patients with end-stage ankle Osteoarthritis (OA). Full details of the background to the trial, the interventions under study and its design are in the published trial protocol [6]. From March 2015 to January 2019, 303 patients were randomised to surgery at one of 17 surgical centres participating in the trial in England, UK.

This article describes the statistical analysis plan for the TARVA trial. Analyses will commence in February 2020 following completion of 52 weeks follow-up for the last patient, data cleaning checks, and data lock. The analysis of the primary outcome will be independently programmed from the cleaned derived dataset by a statistician who did not perform the main analysis, and in parallel by the trial statistician.

### Objectives

The primary objective of the TARVA trial is to compare TAR versus arthrodesis for:
Improvement in self-reported pain-free function from pre-operative assessment (“pre-op”) to 52 weeks after surgery (“post-op”)

The secondary objectives are to compare TAR versus arthrodesis for:
Improvement in self-reported pain, social interaction, physical function, quality of life (QoL), and total ankle range of motion (ROM) from pre-op to 52 weeks post-opImprovement in self-reported pain-free function, pain, social interaction, physical function, and QoL from pre-op to 26 weeks post-opSafety

## Design and methods

### Design

TARVA is a two-arm, prospective, multi-centre, parallel-group, non-blinded randomised controlled trial.

### Patient eligibility criteria

Inclusion criteria:
Diagnosis of end-stage ankle OAAged 50–85 years inclusiveThe surgeon believes the patient is suitable for both TAR and arthrodesis (having considered deformity, stability, bone quality, soft tissue envelope, and neurovascular status)The patient can read and understand the patient information sheet (PIS) and trial proceduresThe patient is willing and able to provide written informed consent

Exclusion criteria:
Previous ipsilateral talonavicular, subtalar, or calcaneocuboid fusion or surgery planned within 1 year of index procedureMore than four lower limb joints fused (including contralateral limb, but excluding PIPJ fusions)Unable to have either an MRI or a CT scan (e.g. severe claustrophobia or contraindication for both types of scan)History of local bone joint infectionSevere osteoporosis (T score < − 2.5) with recent fracture (< 12 months)Any co-morbidity which, in the opinion of the investigator, is severe enough to:
◦ Interfere with the patient’s ability to complete the study assessments◦ Present an unacceptable risk to the patient’s safetyThe patient is participating in another clinical trial that would materially impact on their participation in this study

Patients with end-stage OA in both ankles had only one ankle randomised and operated on as part of the TARVA trial; the other ankle was treated with usual care.

### Randomisation and blinding

The randomisation process was based on a minimisation algorithm. The algorithm gave an overall 85% chance of allocating the patient to the treatment arm which was under-represented with respect to three stratifying variables: surgeon, presence of OA in subtalar joint, and presence of OA in talonavicular joint (as determined by pre-operative MRI scan [7]). The research nurse or delegated individual logged on to the sealed envelope randomisation service and provided patient information (including on stratifying variables) and the surgical treatment to be received was supplied immediately.

Patients were allocated in a 1:1 ratio to the TAR and arthrodesis arms. It was not possible to blind patients, surgeons, radiologists, and clinical assessors for the following reasons: surgeons know what procedure they are performing, radiologists and patients will be able to identify from radiographs which procedure has taken place, and patients who receive ankle arthrodesis and their assessors will invariably know their ankle is stiff (a known consequence of arthrodesis surgery) whereas those undergoing TAR will retain motion in the ankle. To protect against allocation bias, the person recruiting the patient to the study was not aware of the allocation to be assigned prior to contacting the randomisation service.

### Trial intervention

At randomisation patients were allocated to receive either TAR or ankle arthrodesis.

For TAR, the remaining damaged cartilage is removed and the joints are resurfaced with metal implants and an intervening polyethylene liner that is either fixed or mobile to act as a gliding surface. All prostheses are CE-marked.

For ankle arthrodesis, the remaining damaged cartilage is removed from the ends of the bone and the two bones are then held together in compression using screws or plates until they join to become one (bone fusion), so that there is no longer any movement at that joint.

Full details of these interventions can be located in the trial protocol [6].

## Outcomes

### Primary outcome measure

The primary outcome measure is the absolute difference between the two treatment arms in self-reported pain-free function, as measured by the Manchester-Oxford Foot Questionnaire (MOXFQ) walking/standing domain score [8] at 52 weeks post-op. The 52-week score will be used if it was taken in a window from 48 to 56 weeks post-op.

The MOXFQ standing/walking domain score has been found to be a valid and responsive measure to evaluate all types of foot and ankle surgery [9, 10], and it has additionally been shown to be more responsive for the outcomes of foot and ankle surgery patients than generic QoL measures such as the EuroQol five-dimension quality-of-life instrument (EQ-5D) and the Short Form (36) Health Survey (SF-36) [11].

### Secondary outcome measures

The secondary outcome measures for the trial are the absolute differences between the two treatment arms in the:
MOXFQ walking/standing domain score at 26 weeks post-opSelf-reported pain and self-reported social interaction, as measured by the MOXFQ pain and MOXFQ social interaction domain scores at 26 weeks and 52 weeks post-opPhysical function, as measured by the Foot and Ankle Ability Measure Activities of Daily Living (FAAM-ADL) questionnaire at 26 weeks and 52 weeks post-opPhysical function for patients involved in sport, as measured by the FAAM-Sport score at 26 weeks and 52 weeks post-opQoL assessed by the validated EQ-5D (EQ-5D Index and EQ-5D Visual Analogue Scale (VAS)) at 26 weeks and 52 weeks post-opTotal ROM (degrees plantarflexion and dorsiflexion) at 52 weeks post-op, assessed by goniometerProportion of patients experiencing at least one adverse event (AE)Proportion of patients experiencing at least one serious adverse event (SAE)Proportion of patients with recorded complications (including revision surgery and reoperations other than revision)

Additional outcomes are also collected for a detailed cost and cost-effectiveness analysis of TAR versus ankle arthrodesis; however, this analysis will not be performed by the TARVA statistical team so these outcomes are not described here. Further details on the cost effectiveness analysis can be found in the trial protocol [6].

### Calculation of outcome scores

#### The Manchester-Oxford Foot Questionnaire (MOXFQ)

Responses to each MOXFQ questionnaire item consist of a five-point Likert scale ranging from no limitation (scoring 0) to maximum limitation (scoring 4). Items are grouped into three domains: walking/standing (seven items), pain (five items), and social interaction (four items). Domain scores are computed by summing the patient’s responses to each item within the domain and converting to a 0–100 metric, where higher scores represent greater severity.

If a single item within any domain is unanswered it will be imputed with the mean of the respondent’s answers to the other items within that domain. If two or more questions on any domain are unanswered the overall score for that domain will not be calculated and its value will be set to missing [12]. If the entire questionnaire has not been completed all MOXFQ domain scores for that visit will be set to missing.

#### The Foot and Ankle Ability Measure–Activities of Daily Living (FAAM-ADL)

Each of 21 items on the FAAM-ADL are scored from 4 (no difficulty) to 0 (difficulty) [13]. The overall FAAM-ADL score is then calculated by summing the responses to each item completed, dividing this by the maximum score achievable based on the number of items completed (e.g. 84 if all 21 items are completed), and then multiplying the resulting fraction by 100 to return a 0–100 metric, where higher scores indicate a higher level of physical function. If an answer for one item is missing its value will be imputed as the mode of the other items; if more than one item is missing the overall score will be set to missing.

The FAAM-Sport score provides a complementary specific assessment of ability to participate in sports based on eight questionnaire items, each also scored from 0 to 4. A 0–100 metric is then generated using the same approach as for the FAAM-ADL; higher scores indicate a higher level of ability to participate in sports. Missing items will be handled using the same approach as for the FAAM-ADL.

#### EuroQol 5D quality-of-life instrument (EQ-5D)

The EQ-5D assesses current health state across five dimensions—mobility, self-care, usual activities, pain/discomfort, and anxiety/depression—with five levels (each scored 1–5, with higher scores indicating worse health state). EQ-5D dimension scores will be converted to index scores using UK population values [14]. EQ-5D index scores range from − 1 (worse than death) and then 0 (worst health state) to 1 (best health state). The EQ-5D additionally includes a visual analogue scale (EQ VAS), which allows patients to record their overall current health status on a scale ranging from 0 (worst health state) to 100 (best health state).

If any dimension score is missing, the EQ-5D index score will be set to missing. If the entirety of one component of the questionnaire (dimension score or VAS) has not been completed the associated component score will be set to missing. If the entire questionnaire has not been completed, both the EQ-5D index score and EQ-5D VAS at that visit will be set to missing.

## Sample size

The sample size calculation for the primary outcome (change in MOXFQ walking/standing domain by 52 weeks post-op) was performed using Stata/IC version 12.1 [15]. It was based on achieving 90% power to detect the minimal clinically important difference (MCID) in the primary outcome at the 5% level of significance, accounting for expected loss to follow-up. The trial is multi-centre and the outcome plausibly varies by surgeon, so the sample size was adjusted to account for clustering; the intraclass correlation coefficient (ICC) was estimated based on previous studies, and the initially computed sample size was inflated by a factor f = 1 + (m − 1) ∗ ICC [16].

The sample size calculation was partly based on the study by Dawson et al. [9] which defined the MCID in the MOXFQ when evaluating outcomes following surgery for hallux valgus. They defined it as the mean change in MOXFQ of those patients who reported feeling at least “slightly better”, and found it to be 16, 12, and 24, respectively, for the standing/walking, pain, and social interaction domains of the MOXFQ. For this trial we determined it was important to detect a difference of 12 in the change from baseline in MOXFQ standing/walking domain between the two treatment arms; a conservative choice given the threshold for a MCID in the standing/walking domain found in the Dawson et al. study was 16. The standard deviation of the walking/standing domain of the MOXFQ was estimated as 27 [11], and loss to follow-up was estimated as 10% (attrition in similar RCTs has been 5–7% [17]).

Based on these quantities, the required sample size was estimated as 118 patients per arm. Assuming an average cluster size (m) of 14 (patients per surgeon) and an ICC of 0.03 (estimated from the median of ten previous surgical studies reporting patient-reported disease-specific measures 12 months post-surgery [18]), an inflation factor of f = 1.39 was estimated, leading to a final required sample size of 164 per arm or 328 patients total.

The assumptions of ICC = 0.03 and equal numbers of patients per surgeon in the sample size calculation [19] were reviewed by the trial statistician prior to the end of recruitment using the available data. The review indicated lower ICC and also some variability in numbers of patients per surgeon compared to the original assumptions (ICC < 0.01; average cluster size = 15, standard deviation = 9.6), resulting in increased power.

## Analysis principles

### Patient population to be included in analysis

The main analysis will be conducted on an intention-to-treat (ITT) basis; all observed outcome data from patients according to their randomised surgical procedure will be used, irrespective of type of surgery received or whether surgery was performed. Sensitivity analysis (described below) will assess the impact of missing outcome data.

Additionally, if cross-over prior to surgery does occur, a per-protocol (PP) analysis will be performed for the primary outcome that only includes data from patients who undergo surgery according to their randomised surgical procedure. The FAAM-Sport questionnaire is only completed by patients who indicate they are involved in sports. Analysis of the FAAM-Sport domain will therefore always be based on the subgroup of patients who indicate they are involved in sports at baseline, following the above principles.

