### Trial treatment

The number of patients undergoing their randomised surgery will be reported by treatment group. Although it is made explicit that patients cannot change surgical treatment arm once it has been randomly allocated, the clinician remains free to give alternative treatment to that specified in the protocol if it is felt to be in the best interest of the patient. Any cross-overs or other treatment deviations, as well as the number of patients who did not undergo surgery of any kind, will be specified along with reasons, as detailed in the protocol deviation log.

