##### Adverse events, serious adverse events, and complications

The following absolute differences in proportions will be estimated using the treatment coefficient obtained from a binomial regression model with the identity link function:
Proportion of patients experiencing at least one AEProportion of patients experiencing at least one SAEProportion of patients with at least one recorded complication (any complication)Proportion of patients requiring revision ankle surgeryProportion of patients experiencing reoperation other than revisionProportion of patients experiencing surgical site infection

Relative risks will be obtained from a binomial regression model with the log link. If convergence is an issue a Poisson regression model with the log link and robust error estimates will alternatively be fitted to obtain relative risks.

Unadjusted treatment differences will initially be obtained for each of the event outcomes. The models will then be extended to adjust for presence of OA in each of the two adjacent joints (OA1, OA2). Due to potential sparse data in these outcomes, the models will not adjust for surgeon.

The distribution of the AEs and SAEs per patient will also be presented descriptively, but no formal analysis will be performed.

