## Abbreviations

AE: Adverse event
AP: Anteroposterior
CT: Computed tomography
EQ-5D: EuroQol five-dimension quality-of-life instrument
FAAM: The Foot and Ankle Ability Measure
FAAM-ADL: The Foot and Ankle Ability Measure Activities of Daily Living subscale
FAAM-Sport: The Foot and Ankle Ability Measure Sport subscale
ICC: Intra-class correlation coefficient
ITT: Intention-to-treat; includes all observed data from randomised patients in accordance with their randomised procedure, regardless of whether surgery actually occurred
m: Average cluster size (patients per surgeon)
MAR: Missing-at-random
MCID: Minimal clinically important difference
MI: Multiple imputation
MNAR: Missing-not-at-random
MOXFQ: The Manchester-Oxford Foot Questionnaire
MRI: Magnetic resonance imaging
OA: Osteoarthritis
PIS: Patient information sheet
QoL: Quality of life
ROM: Range of motion
SAE: Serious adverse event
TAR: Total ankle replacement
TARVA: Total Ankle Replacement Versus Arthrodesis trial
T-score: A measurement of bone density expressed in standard deviation units from that of a healthy young adult
UCL CCTU: UCL Comprehensive Clinical Trials Unit
VAS: Visual analogue scale

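### Complications, revision, reoperation and surgical site infection have only an as-randomised comparison; a labelled analysis of operated patients by procedure received should stand beside it

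*SAP article*

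**What the plan says.** Under Patient population to be included in analysis, the SAP article sets intention-to-treat as the basis of the main analysis: observed outcome data are used by randomised procedure, "irrespective of type of surgery received or whether surgery was performed". The Abbreviations section repeats the rule; the set "includes all observed data from randomised patients in accordance with their randomised procedure, regardless of whether surgery actually occurred".

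One alternative set is named. If cross-over before surgery occurs, "a per-protocol (PP) analysis will be performed for the primary outcome", restricted to patients who had the operation they were randomised to. No other outcome gets it.

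Under Adverse events, serious adverse events, and complications, six proportions (any AE, any SAE, any complication, revision, other reoperation, surgical site infection) have risk differences "estimated using the treatment coefficient obtained from a binomial regression model with the identity link function". Relative risks come from a log-link model. No denominator, operated-patient set or as-treated set is given there. Secondary outcome measures defines the complication outcome as "Proportion of patients with recorded complications".

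Under Trial treatment, the plan accepts that "the clinician remains free to give alternative treatment to that specified in the protocol" when this is judged best for the patient. It undertakes to report cross-overs and other deviations, and "the number of patients who did not undergo surgery of any kind", with reasons.

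**The concern.** Safety of TAR versus arthrodesis is a stated secondary objective. Revision, reoperation and surgical site infection are consequences of an operation, and many readers will want the risk that goes with having each one. The planned comparison answers a different question: the risk that goes with being allocated to each one. The two answers coincide only if everyone has the allocated operation.

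Neither kind of deviation is remote, because the plan provides for both. A patient who switches contributes any complication to the randomised arm. A patient who is never operated on remains in the intention-to-treat set but cannot have a complication of the trial operation. For harms, dilution towards no difference is the less cautious direction, and an imbalance in non-operation could exaggerate or hide a difference. The plan adds a received-procedure check for function but none for the outcomes most directly tied to the operation.

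**Working it through.** **Text check.** The population section gives a general rule (as randomised) and one exception set (per-protocol, primary outcome only). The event-outcome section adds no population of its own. The plan does make exceptions where it wants them: FAAM-Sport is analysed in patients involved in sport at baseline, and the trigger for the missing-not-at-random analysis is counted among patients operated on. No such exception appears for the event outcomes. If the general rule were read as covering the primary outcome alone, the event models would have no defined population, and a sentence would still be needed.

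**Inputs.** From the document: "303 patients were randomised to surgery" at 1:1, so 303 / 2 = 151.5, taken as 151 per arm. The plan states no complication, cross-over or non-operation rate, so there is no figure of its own to reproduce. All rates below are assumptions, and which procedure has the higher risk is arbitrary.

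**Formula.** Let p_T and p_A be the risks by procedure received, u the share of an arm never operated on (taken as event-free), and c the share that crosses over:

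- TAR arm: r_T = (1 − u_T − c_T) × p_T + c_T × p_A
- Arthrodesis arm: r_A = (1 − u_A − c_A) × p_A + c_A × p_T

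Example, with 10% never operated and 5% crossed over in each arm: r_T = 0.85 × 30% + 0.05 × 20% = 26.5%; r_A = 0.85 × 20% + 0.05 × 30% = 18.5%; difference 8.0 points.

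| Risk by procedure received (TAR v arthrodesis) | Never operated (TAR / arthrodesis) | Cross-over, each arm | As-randomised risks | Difference (points) | Relative risk |
|---|---|---|---|---|---|
| 30% v 20% | 0 / 0 | 0 | 30.0% v 20.0% | 10.0 | 1.50 |
| 30% v 20% | 5% / 5% | 0 | 28.5% v 19.0% | 9.5 | 1.50 |
| 30% v 20% | 10% / 10% | 0 | 27.0% v 18.0% | 9.0 | 1.50 |
| 30% v 20% | 0 / 0 | 5% | 29.5% v 20.5% | 9.0 | 1.44 |
| 30% v 20% | 10% / 10% | 5% | 26.5% v 18.5% | 8.0 | 1.43 |
| 30% v 20% | 2% / 10% | 0 | 29.4% v 18.0% | 11.4 | 1.63 |
| 30% v 20% | 10% / 2% | 0 | 27.0% v 19.6% | 7.4 | 1.38 |
| 20% v 20% | 2% / 10% | 0 | 19.6% v 18.0% | 1.6 | 1.09 |

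With 10% v 5% (difference 5.0, relative risk 2.00), the as-randomised difference runs from 4.0 to 5.3 points over the same scenarios.

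Three features stand out. Equal non-operation shrinks the risk difference but leaves the relative risk unchanged. Cross-over pulls both towards no difference. Unequal non-operation moves both in either direction.

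**Scale against sampling error.** With 151 per arm, the half-width of a 95% interval for the risk difference is:

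- at 15% in both arms: 1.96 × √(2 × 0.15 × 0.85 / 151) = 8.1 points
- at 30% v 20%: 1.96 × √((0.30 × 0.70 + 0.20 × 0.80) / 151) = 9.7 points
- at 20% in both arms: 1.96 × √(2 × 0.20 × 0.80 / 151) = 9.0 points

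The largest shift at 30% v 20% is 10.0 − 7.4 = 2.6 points, about a quarter of 9.7. The spurious 1.6 points at equal risks is under a fifth of 9.0.

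**The case against.** The as-randomised comparison is not a mistake. The secondary outcomes are defined as differences between treatment arms, and analysis by allocation answers that question with the protection of randomisation. A reader might infer that the plan attributes complications to the wrong procedure. It does not: it estimates the effect of a treatment policy, which is legitimate. This part of the objection stands in full.

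A reader might also infer that the plan counts never-operated patients as event-free. Nowhere is this written. It is a close inference, because these patients stay in the set and the outcome is a recorded complication. But the event section gives no denominator, and a rule based on observed outcome data could leave out someone who withdrew before surgery. What can be said is that the denominator is not stated.

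The supplementary analysis has a weakness of its own. Alternative treatment is given on a judgement about the individual patient, so grouping by procedure received invites confounding by indication. Leaving out unoperated patients is a post-randomisation exclusion. The table treats risk by procedure received as unrelated to switching, so its reference difference is the right answer only by construction.

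The plan also covers part of the ground. Reporting deviations and unoperated patients, with a CONSORT flowchart, should make an imbalance visible. If non-operation were the only deviation, crude proportions could be rescaled: 29.4% / 0.98 = 30% and 18.0% / 0.90 = 20%. This does not work for cross-over, where a reader would need event counts by procedure received.

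Finally, an article may leave detail to a fuller plan or to supplementary tables that are not at hand. That would be decisive if the article were silent. It instead states the population rule and limits the only alternative set to the primary outcome.

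**Conclusion.** The point holds as a modest, inexpensive improvement. Followed as written, the plan yields no comparison of complications, revision, reoperation or surgical site infection by procedure performed, although it foresees the deviations that make such a comparison informative. For procedure-specific risk, the as-randomised difference may be diluted, or shifted if non-operation differs between arms.

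The size is not known. It depends on rates that the document does not give, and it is zero if no deviations occur. Under the assumed rates, with never-operated patients taken as event-free and switching unrelated to risk, a 10-point difference becomes 7.4 to 11.4 points. That is small beside an interval half-width of about 8 to 10 points.

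It would be tempting to extend the argument to all AEs and SAEs. The documents do not support that, because a patient who is never operated on can still have an adverse event. The point is limited to events that can only follow an operation.

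**What to change.** Keep the as-randomised comparison and describe it as a treatment-policy estimate. Then make two changes to the section on adverse events, serious adverse events and complications:

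1. State the denominator for each event outcome, including whether a patient who was never operated on contributes a non-event or is left out.
2. For any complication, revision, other reoperation and surgical site infection, add a supplementary analysis with the same models in operated patients grouped by procedure received. Show it side by side with the as-randomised results, with numbers and events for each group.

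Label the second analysis as non-randomised and open to confounding by indication, so that it is not read as replacing the first. The cost is a sentence or two in the plan, one extra table and that caveat. No new data are needed beyond the record of surgery performed, which the plan already undertakes to report. If there are no cross-overs and no unoperated patients, the two analyses coincide and the table can be dropped.
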